##### Infant testing outcomes

The completeness and efficiency of fulfillment of Kenyan EID testing guidelines upon implementation of birth and POC testing at study sites will be measured (Table 1). Measures of completeness will include proportions of birth and 6-week tests with results returned and with mothers notified of results. Additionally, we will track “complete retention,” the proportion of mothers who are notified of results from specimens collected in both the birth and 6-week windows. Measures of efficiency include turnaround time (TAT) associated with key steps in POC or HIV DNA PCR-based diagnosis: TAT from specimen collection to result availability, TAT from result availability to mother notification of results, and overall TAT from specimen collection to mother notification. Infant age at completion of each step of diagnosis (and at ART initiation if testing HIV-positive) will be further measures of EID efficiency that imply clinical timeliness of the specific EID steps.

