## Background

In 2015, an estimated 110,000 new pediatric human immunodeficiency virus (HIV) infections occurred in the 21 Global Plan priority countries [1]. Infant survival and the success of antiretroviral therapy (ART) treatment of HIV-positive infants are associated with early infant age at initiation [2]; thus, early HIV testing, diagnosis, and prompt ART initiation are crucial. In 2015, an estimated 6600 children were infected with HIV in Kenya, a 55% decrease since 2009, but the country’s rate of HIV-exposed infants receiving a routine HIV DNA polymerase chain reaction (PCR) test by 2 months of age has stagnated near 50% since 2011 [3, 4].

One barrier to successful early infant diagnosis (EID) is the waiting time for test results. The sequence of EID services involves multiple time-sensitive steps requiring coordination between medical provider, diagnostic laboratory, and mother/caregiver (“mother”). The standard EID algorithm in Kenya includes mother acceptance of infant testing; specimen collection, transport, and laboratory analysis; communication of results to healthcare providers and caregivers; and linkage to care, including opportunistic infection prophylaxis for all HIV-exposed infants and ART for HIV-positive infants [5]. All steps are susceptible to delays and patient loss to follow-up [5–7]. Traveling long distances for clinical care adds logistical and resource barriers to successful HIV treatment [8].

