#### Study outcomes

##### Acceptability and uptake

Key informant interviews will document attitudes, preferences, perceived benefits, and concerns from the perspective of stakeholders (HIV-positive mothers, EID providers, community members) (Table 1). Uptake of testing, by POC and SOC methods, will be quantified in terms of proportions of infants who are tested (have a documented specimen collection) in the birth and 6-week windows and the proportion of infants determined HIV-negative at birth who are presented again for retesting in the 6-week window.

**Table 1 Tab1:** Implementation and feasibility measures

Variable	Measure (for both POC and HIV DNA PCR tests, unless specified)	EID stage(s)
Acceptability/uptake	Mothers’ views of birth testing impact on infant, family	
	Provider recommendations/concerns on implementation	
	Community member attitudes and recommendations	
	Proportion (%) infants with specimen collected	Birth, 6 weeks^a^
	Median infant age at specimen collection	Birth, 6 weeks
	% Birth-tested infants returned for 6-week retest	Sequential
Infant testing outcomes	% Tests with results returned	Birth, 6 weeks
	% Tests with mother notified of results	Birth, 6 weeks
	Median turn-around time (TAT), specimen to test result availability	Birth, 6 weeks
	Median infant age at result availability	Birth, 6 weeks
	Median TAT, result availability to mother notification of results	Birth, 6 weeks
	Median overall TAT, specimen to mother notification of results	Birth, 6 weeks
	Median infant age at mother notification of results	Birth, 6 weeks
	Median infant age at ART initiation (if diagnosed HIV+)	Birth, 6 weeks
	Complete retention: % mothers notified of birth and 6-week results	Sequential
POC platform performance	Number failed POC tests, GeneXpert and Alere q	Pooled
	Number POC missed opportunities due to machine breakdown	Pooled
	Number POC missed opportunities due to machine error	Pooled
	Number POC missed opportunities due to cartridge stockout	Pooled
	Concordance of POC results (each platform) with HIV DNA PCR	Birth, 6 weeks
Provider feedback	Acceptability and feasibility of implementing birth and POC testing	
	Benefits and challenges of birth and POC testing for patients	
Costs of POC implementation	Acquisition of GeneXpert and Alere q machines	
	Acquisition of accessory equipment	
	Site-specific training, secure storage	
	Acquisition of test cartridges	
	Maintenance and repair of machines	

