### Statistical analysis

This study is designed to gather preliminary outcome data to inform implementation guidance and pilot data for a subsequent larger study. We anticipate mean monthly enrollment per study site of approximately 15 eligible participants, yielding an estimated total enrollment of 720 mother-infant pairs by the end of the 12-month intervention phase. Reductions in study participation are expected to result from documented transfer to other facilities, loss to follow-up, miscarriage, and infant mortality prior to testing. Nonetheless, we anticipate ample power to describe and compare outcomes of birth testing and between POC and PCR testing strategies to estimate effect sizes and an intracluster correlation coefficient (ICC) to inform future sample size and power calculations.

Categorical variables will be presented as proportions, and continuous variables as means (SD) or medians (IQR) depending on the distribution of data. Quantitative measures compared across POC platforms or between POC and HIV DNA PCR testing methods will be analyzed using parametric and non-parametric (Exact or Wilcox and Rank-sum) tests.

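### Turnaround times and ages at each step have values only for completed tests, so POC–PCR comparisons of medians would rest on different subsets of the same infants

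*Protocol article*

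**What the plan says.** All references are to the protocol article.

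- **Infant testing outcomes.** Efficiency is measured by TAT for each step, including "overall TAT from specimen collection to mother notification", and by age: "Infant age at completion of each step of diagnosis (and at ART initiation if testing HIV-positive) will be further measures of EID efficiency".
- **Table 1.** The summaries are medians, such as "Median overall TAT, specimen to mother notification of results" and "Median infant age at mother notification of results", for both POC and PCR and for both testing windows. No denominator is given for any median.
- **Completeness, in the same section.** "Measures of completeness will include proportions of birth and 6-week tests with results returned and with mothers notified of results". Complete retention across the two windows is also planned.
- **Statistical analysis.** The plan is to present "continuous variables as means (SD) or medians (IQR) depending on the distribution of data" and to compare POC with PCR by parametric, exact or rank-sum tests. No rule is given for tests that never reach a step, and no method for censored times is named.
- **Background.** On the diagnostic sequence: "All steps are susceptible to delays and patient loss to follow-up".
- **Birth testing.** The POC result is to reach the mother that day, or before discharge, within 24 h. The PCR specimen and its paper result travel by courier, and the mother is then called back.

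**The concern.** A TAT that ends at notification does not exist for a mother who is never told, and an age at completion does not exist for a step never completed. A median or rank-sum test on the recorded values therefore describes only completed tests.

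POC and PCR are run in parallel on the same infants, which should make the contrast a fair one. Completer-only summaries undo that, because the infants with a completed POC test and those with a completed PCR test need not be the same. The PCR route has more points at which a test can be lost (two courier legs and a return visit). If it does lose more, its median is taken over a more selected group and its delay is understated relative to time to notification for every infant tested.

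Efficiency of services is a listed objective. The Statistical analysis and Discussion sections also intend the results to supply effect sizes for a later, larger trial, and a selected contrast would carry over into that design. Age at ART initiation has the same feature: a diagnosed infant who never starts has no value.

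**Working it through.** **The plan's own figure.** The article gives no TAT, loss rate or power figure. Its one sample-size figure reproduces: 15 per site per month × 4 sites × 12 months = 720 pairs.

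**Inputs for the illustration.** All are assumed, because the documents give none: the share c of tests that reach notification, and the shape of the completers' times (lognormal with log-SD 0.5, 0.8 or 1.0, or exponential).

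**Step 1: never-notified tests counted as still waiting.** Half of all tests are notified when a fraction q = 0.5/c of the completers has been notified. The all-tests median is therefore the q-quantile of the completers' times. Its ratio to the completers' median is

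- lognormal: exp(σ · z_q), with z_q the standard normal quantile at q;
- exponential: ln(1 − q) / ln(0.5).

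Example with c = 0.80: q = 0.5/0.80 = 0.625. The exponential ratio is ln(0.375)/ln(0.5) = 1.42, and the lognormal ratio with σ = 0.5 is 1.17.

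| Loss | c | q | σ = 0.5 | σ = 0.8 | σ = 1.0 | Exponential |
|---|---|---|---|---|---|---|
| 5% | 0.95 | 0.526 | 1.03 | 1.05 | 1.07 | 1.08 |
| 10% | 0.90 | 0.556 | 1.07 | 1.12 | 1.15 | 1.17 |
| 20% | 0.80 | 0.625 | 1.17 | 1.29 | 1.38 | 1.42 |
| 30% | 0.70 | 0.714 | 1.33 | 1.57 | 1.76 | 1.81 |
| 40% | 0.60 | 0.833 | 1.62 | 2.17 | 2.63 | 2.58 |
| 50% or more | ≤ 0.50 | ≥ 1 | not reached | not reached | not reached | not reached |

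Since q is never below 0.5, the completers' median cannot exceed the all-tests median under this definition.

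**Step 2: loss falls on the longest delays (exponential times).** The completers' median divided by the true median is −ln(1 − 0.5c)/ln 2. At c = 0.95, 0.90, 0.80, 0.70 and 0.60 this is 0.93, 0.86, 0.74, 0.62 and 0.51.

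**Step 3: loss unrelated to delay, target the delay among the notified.** In simulation the completers' median stays at 1.00 of the underlying median for c = 0.9, 0.7 and 0.5.

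Whether the median is shortened, and by how much, thus depends on the loss rate, the reason for loss and the quantity of interest.

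**The case against.** The strongest reply has four parts.

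1. **No passage restricts the medians to completed tests.** A reader might infer that the plan states such a restriction; it does not. A denominator could be set in a fuller plan that is not shown. This stands as to certainty. What remains is that the measures, as defined, have no value without completion.
2. **Infants never notified are not lost from the study.** A reader might infer that they vanish from the results. They do not: they count in the completeness proportions, which Table 1 lists beside the medians. Reporting yield, and then time among those reached, is an established way to present a care cascade. This stands too, but those proportions do not change a rank-sum test or an effect size computed on completers.
3. **The named methods do not rule out an all-tests analysis.** A median or rank-sum test can rank never-notified tests last. That is correct, but the article does not say it will be done.
4. **Bias is not shown.** A reader might infer that PCR will certainly lose far more tests, that the slowest cases are the ones lost, or that results pending at a data cut-off are discarded. The documents give no loss rate, no link between loss and delay, and no cut-off. POC has failures of its own, including failed tests and an Alere q cartridge stock-out. Step 3 shows a case with no shortening.

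The effect would also be conservative for POC and is unlikely to reverse the contrast. With an assumed completers' median of 28 days, log-SD 0.6 and 30% loss, the PCR median over all tests is 28 × exp(0.6 × z at 0.714) = 39.3 days, against POC results planned within 24 h. This limits the consequence mainly to the size of the effect passed on to the later trial.

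**Conclusion.** The concern holds in a limited form. As defined, TAT and age at each step exist only for completed tests, so POC–PCR comparisons of their medians would naturally rest on different subsets of one cohort. The separate completeness figures reveal unequal loss without correcting the comparison. If PCR loses more tests, the contrast understates PCR delay relative to time to notification for all infants tested. The two notification routes make such loss plausible, but no rate is given.

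The size cannot be fixed from the documents. Under the assumed lognormal or exponential times, with never-notified tests counted as still waiting, the all-tests median is longer by about 3–8% at 5% loss, 17–42% at 20% and 62–163% at 40%. It is not reached once half or more are lost. If the target is delay among the notified and loss is unrelated to delay, nothing is shortened. The point is worth acting on because timeliness of the service concerns every infant tested and the remedy is cheap.

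**What to change.** - For specimen to result, specimen to notification, and the matching infant ages, add the cumulative proportion completed with every collected specimen in the denominator. Censor incomplete tests at last follow-up and treat death and transfer as competing events. Take last follow-up as the last date on which site records were checked. Censoring at the mother's last visit would assume that loss is unrelated to delay.
- Report the percentage notified by fixed days, and read the median from the curve, stated as not reached if the curve stays under 50%.
- Base the POC–PCR effect size for the later trial on these quantities.
- Keep completer-only medians as secondary, each shown with its denominator and matching completeness proportion. The step from result to notification remains conditional on a returned result, because a test without a result has no starting point.

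**Cost.** A little more analysis. The Data collection section already lists dates of specimen collection and return of results, and the recording of mothers' notification. The downside is that some medians become longer or are not reached.

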##### POC platform performance

Assessment of both the Xpert and Alere q HIV POC platforms will include evaluation of testing reliability (Table 1). Measures to be tracked include number of failed tests (and wasted cartridges), and number of missed opportunities to engage infants with POC testing due to documented machine breakdown, machine error, or cartridge stockout. The anticipated number of HIV-positive infants identified is too small to support robust sensitivity or specificity calculations, but we will track concordance between test results from each POC platform and the corresponding HIV DNA PCR results.

##### EID provider feedback

Provider interviews conducted during the pilot study will solicit provider feedback on challenges faced in implementing birth and POC testing, including matters of personnel training, optimizing workflow, engagement of mothers, management of cartridge supply, and technical challenges. Providers’ views of the benefits and risks of birth and POC testing for patients will be recorded.

##### Costs of POC testing implementation

Cost measures to be tracked and analyzed for each of the POC test platforms include up-front purchase of machines and accessory equipment; site-specific training and secure equipment storage; purchase of test cartridges, including delivery and customs fees; and machine repair.

### Statistical analysis

This study is designed to gather preliminary outcome data to inform implementation guidance and pilot data for a subsequent larger study. We anticipate mean monthly enrollment per study site of approximately 15 eligible participants, yielding an estimated total enrollment of 720 mother-infant pairs by the end of the 12-month intervention phase. Reductions in study participation are expected to result from documented transfer to other facilities, loss to follow-up, miscarriage, and infant mortality prior to testing. Nonetheless, we anticipate ample power to describe and compare outcomes of birth testing and between POC and PCR testing strategies to estimate effect sizes and an intracluster correlation coefficient (ICC) to inform future sample size and power calculations.

Categorical variables will be presented as proportions, and continuous variables as means (SD) or medians (IQR) depending on the distribution of data. Quantitative measures compared across POC platforms or between POC and HIV DNA PCR testing methods will be analyzed using parametric and non-parametric (Exact or Wilcox and Rank-sum) tests.

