**Methods:**

We will pilot the implementation of birth testing by HIV DNA PCR, as well as two POC testing systems (Xpert HIV-1 Qual [Xpert] and Alere q HIV-1/2 Detect [Alere q]), on specimens collected from Kenyan infants at birth (0 to 2 weeks) and 6 weeks (4 to < 24 weeks) postnatal. The formative phase will inform optimal implementation of birth testing and two POC testing technologies. Qualitative interviews with stakeholders (providers, parents of HIV-exposed infants, and community members) will assess attitudes, barriers, and recommendations to optimize implementation at their respective sites. A non-blinded pilot study at four Kenyan hospitals (*n* = 2 Xpert, *n* = 2 Alere q platforms) will evaluate infant HIV POC testing compared with standard of care HIV DNA PCR testing in both the birth and 6-week windows. Objectives of the pilot are to assess uptake, efficiency, quality, implementation variables, user experiences of birth testing with both POC testing systems or with HIV DNA PCR, and costs.

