### Phase 2: intervention

#### Study design

We will pilot the implementation of POC and birth testing at four government hospitals over a 12 month period. The four study sites will be randomized, using a random number generator, to pilot one of the two POC systems (Xpert HIV-1 Qual for HIV RNA or Alere q HIV-1/2 Detect). SOC diagnostic testing (HIV DNA PCR test on DBS samples) will be conducted in parallel at all study sites, including the newly introduced birth testing time point. Patient flow in the pilot is diagrammed in Fig. 1.

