POC testing also offers potential to improve EID system efficiency in low resource settings where there are multiple delays inherent in the laboratory-based HIV DNA PCR testing process. Sample testing in the clinic setting potentially facilitates mother notification of infant HIV status on the same day as test. To fully realize the POC technology’s potential at the true point of care, cadres of clinical providers must be trained to perform diagnostic procedures outside of traditional clinical duties. Therefore, in addition to traditional laboratory personnel, our pilot study includes training nurses to conduct POC testing within the Maternity and MCH settings. This pilot will solicit provider feedback regarding issues of patient flow, interdepartmental collaboration, and provider workload, while identifying potential barriers to this task-shifting approach during larger scale-up. Other performance measures reflecting the utility of POC platforms—such as user friendliness, equipment durability, test failure rate, costs of maintenance, and frequency of cartridge stockouts—will likely affect the consistency of testing operations and missed opportunities for diagnosis. This pilot study will track these variables and thus supply preliminary feasibility data to inform effective and sustainable POC interventions for larger future studies.

These novel data on implementation outcomes and clinical impact of birth HIV testing with POC and PCR testing strategies are timely given the movement toward more rigorous EID in low resource countries. Implementation and user satisfaction data from the two approved POC platforms, GeneXpert and Alere q, may also guide other groups considering investment in POC scale-up. By providing parameters to estimate effect size and intraclass correlation, these results will facilitate the design of properly powered pragmatic trials to evaluate the impact of birth and POC HIV testing in Kenya. These timely data may also facilitate wider adoption of 2016 EID guidelines issued by WHO and the government of Kenya to accelerate infant testing within the existing PCR infrastructure, while bridging the birth testing strategy to implementation of POC testing technologies.

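### The claim of ample power should not extend to the ICC: with four sites its precision is set by 2 or 3 between-site degrees of freedom, not by 720 pairs

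*Protocol article*

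**What the plan says.** The sample-size paragraph (Protocol article, Statistical analysis) gives a recruitment rate of about 15 per site per month and a total: "yielding an estimated total enrollment of 720 mother-infant pairs by the end of the 12-month intervention phase". It then concedes losses of unstated size: "Reductions in study participation are expected to result from documented transfer to other facilities, loss to follow-up, miscarriage, and infant mortality prior to testing". The next sentence reads "Nonetheless, we anticipate ample power to describe and compare outcomes of birth testing and between POC and PCR testing strategies" and continues "to estimate effect sizes and an intracluster correlation coefficient (ICC) to inform future sample size and power calculations". No ICC value, interval width, effect size or power figure accompanies the claim.

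The Discussion returns to the same use: "By providing parameters to estimate effect size and intraclass correlation, these results will facilitate the design of properly powered pragmatic trials".

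The number of clusters is fixed in the Phase 2 study design: "The four study sites will be randomized, using a random number generator, to pilot one of the two POC systems". The abstract gives the split as two hospitals per platform.

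**The concern.** The power claim is argued from the number of participants: the paragraph states the total, admits losses and says that power is ample all the same. That reasoning can serve a comparison made within infants. It does not serve an ICC, which is a statement about variation between sites and can be no better known than the number of sites allows.

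The ICC matters here because the article names it as something the pilot will hand to its successor. If a later trial takes the estimate as reliable, its design effect, and so its sample size, inherits the error. The number of sites is not acknowledged as a limit. By contrast, the section on POC platform performance openly says that the expected number of HIV-positive infants is too small for robust sensitivity and specificity.

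**Working it through.** **The plan's own figure.** 15 per site per month × 4 sites × 12 months = 720, so the stated total reproduces. With equal recruitment this is 720 / 4 = 180 per site. The power claim has no stated inputs and cannot be reproduced.

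**Inputs.**
- From the article: k = 4 sites, two per platform; m = 180 per site.
- Assumed, because the article gives no values: observed ICCs of 0.02 and 0.05; m = 90 to represent 50% attrition; 50 infants per site in a future trial.

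**Method.** One-way random-effects ICC with its F-based 95% interval. This is a normal-theory approximation for outcomes that are proportions.
- F = (1 + (m − 1)·ICC) / (1 − ICC)
- Limits: (F/Fq − 1) / (F/Fq + m − 1), where Fq is the 97.5% quantile for the lower limit and the 2.5% quantile for the upper.
- Between-site df = 4 − 1 = 3, or 4 − 2 = 2 with platform fitted. Within-site df = 720 − 4 = 716.

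**Observed ICC 0.05, m = 180.** F = (1 + 179 × 0.05) / 0.95 = 10.47.
- 3 df: quantiles 3.134 and 0.0719. Lower: 10.47/3.134 = 3.34, so 2.34/182.34 = 0.013. Upper: 10.47/0.0719 ≈ 145.7, so 144.7/324.7 = 0.446.
- 2 df: quantiles 3.708 and 0.0253. By the same steps, 0.010 to 0.696.

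**Observed ICC 0.02, m = 180.** F = (1 + 179 × 0.02) / 0.98 = 4.67.
- 3 df: 0.003 to 0.262.
- 2 df: 0.001 to 0.505.

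**Does the number of infants matter?** With m = 90 and an observed ICC of 0.05, the interval is 0.009 to 0.467 (3 df) or 0.006 to 0.715 (2 df). Halving enrolment moves the upper limit from 0.446 to 0.467, or from 0.696 to 0.715. By contrast, at 180 per site, an interval of total width 0.10 around 0.05 would need about 15 sites.

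**How often the estimate misleads.** In a simulation of 400,000 draws at 180 per site, a true ICC of 0.05 gave an estimate below half its value 34% (3 df) to 41% (2 df) of the time.

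**Consequence for the next trial.** Design effect = 1 + (50 − 1)·ICC.

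| Basis | ICC used | Design effect |
|---|---|---|
| Planned | 0.05 | 3.45 |
| 3 df limits | 0.0128 to 0.4456 | 1.63 to 22.8 |
| 2 df limits | 0.0100 to 0.6963 | 1.49 to 35.1 |

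Against the planned value:
- Too small by up to 22.8/3.45 = 6.6-fold (3 df) or 35.1/3.45 = 10.2-fold (2 df).
- Too large by up to 3.45/1.63 = 2.1-fold (3 df) or 3.45/1.49 = 2.3-fold (2 df).

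**The case against.** The strongest reply concerns what the sentence says. Grammatically, ample power first governs describing and comparing outcomes; effect sizes and the ICC follow as what that work yields. POC and PCR are run on samples from the same infants at every site, so that comparison is paired and much less limited by the number of sites. This stands, and the point is confined to the ICC for that reason. It does not rescue the ICC, because the same sentence carries the claim on to it and the Discussion repeats the use.

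The article also calls its data preliminary and says only that the estimates will inform or facilitate later design. Nothing says that a bare point ICC will be the sole input. That is fair, and the consequence above is conditional on planning from the point estimate. A pilot label excuses imprecision, but it does not make a claim of ample power true.

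The article does not say that the ICC will be adjusted for platform. Several outcomes are measured by PCR at all four sites, where 3 df is a natural choice, so both sets of figures are shown. How the ICC is estimated and reported can be left to an analysis plan. The point here is a stated property that no analysis plan could supply with four sites.

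A reader might infer that the ICC would be wholly unknown, or that the next trial could be wrong by a factor of tens in either direction. The figures support neither. At full enrolment the lower limit already excludes zero at an observed ICC of 0.02. The 24-fold span of design effects (35.1/1.49) compares the two ends of the 2-df interval with each other, not with the planned value.

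**Conclusion.** The point holds for the ICC. Four sites cannot deliver an ICC precise enough to plan on by itself, and recruiting all 720 pairs does little to change that. At an observed 0.05 the upper limit is about 9 times (0.446/0.05) or 14 times (0.696/0.05) the estimate. A trial planned on it at 50 per site could be about 7- to 10-fold too small, or about 2-fold too large, at the edges of a 95% interval.

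These sizes rest on illustrative ICC values, equal recruitment, a normal-theory approximation and an assumed future cluster size. The dependence on the number of sites rather than infants does not turn on the particular ICC chosen. The documents give no ground for reading this as a fault in the paired POC versus PCR comparison.

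**What to change.** In Statistical analysis, end the power claim before the ICC and leave the wording on the paired POC versus PCR comparison as it is. Then add a sentence such as: *With four sites the ICC is exploratory and will be reported with its 95% confidence interval; future sample sizes will be planned over a range of ICC values, including external estimates, and not on this point estimate alone.*

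Soften the Discussion sentence to match, for example by saying that the results will contribute to the range of ICC values considered when later trials are designed.

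The cost is two sentences, with no change to sites, recruitment, outcomes or conduct. The downside is a less favourable statement of what the pilot delivers.
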